#### WASI-ll

The WASI-II [47] is an individual, clinician-administered measure of cognitive intelligence based on the Wechsler Adult Intelligence Scale - Fourth Edition (WAIS-IV) [54]. The WASI-II includes 4 subtests: block design, vocabulary, matrix reasoning, and similarities. It produces 3 metrics: Full-Scale IQ, Verbal IQ, Performance IQ. The WASI-II correlates highly with the WAIS-IV and has good reliability and validity [55].

#### AQ-10

The AQ-10 [42] is a short-form, 10-item, self-assessment instrument for measuring autistic traits based on the AQ-10 [56]. Each of the 10 items contains a statement such as “I find it easy to 'read between the lines' when someone is talking to me.” Responses are made on a 4-point scale ranging from “Definitely Agree” to “Definitely Disagree.” One point is scored if the respondent selects “Definitely Agree” or “Slightly Agree” on each of items 1, 7, 8, and 10. One point is scored for “Definitely Disagree” or “Slightly Disagree” on each of items 2, 3, 4, 5, 6, and 9*.* The AQ-10 has good construct validity and adequate internal consistency with a Cronbach alpha of .85 [42].

#### Questionnaire of Task Satisfaction

In addition to these measures, a self-developed questionnaire of satisfaction, acceptance, and enjoyment of the task will also be designed to assess how viable this method of training is for people with alexithymia and ASD (Multimedia Appendix 2). It will include 5 statements about the study task, with responses on a 5-point scale. Responses will range from 1 (Not very true) to 5 (Very true). Higher scores for each question indicate that the statement applied more strongly to the individual. Examples of the items are “The task made me uncomfortable” and “I feel like this task helped me.”

### Equipment

The Tobii Pro x3-120 Eye Tracker (TPX3) is a screen-based eye tracker that tracks the gaze point on a screen. The TPX3 has been certified to meet European standard EN 62471, which indicates that it is not harmful to the human eye. The TPX3 has a sampling rate of 120 Hz and a large head movement box (area where the user’s head can move and still be tracked). Only the gaze point 2D coordinates on the screen for each eye will be used. The TPX3 will attach to the bottom of a computer monitor that is ~64 cm in front of the participant. Both the chair and the participant’s screen can adjust for height to make sure the participant’s head is within the head movement box as indicated in Figure 1. The chair and screen height will be adjusted based on the setup procedure within the iMotions software prior to running the iMotions software eye-tracker calibration process.

**Figure 1 figure1:**
[figure not shown]
Physical layout of experiment and eye-tracker.

### Primary Outcome

The primary outcome being assessed is an increase in FEER. This will be measured by comparing the percent of correctly identified facial emotion expressions from the baseline assessment task to the instructed mimicry experimental task. Additionally, the percent of correctly identified expressions will also be compared between the control condition and the intervention condition. This will provide 2 primary metrics: before-after percent improvement and control group to experimental group percent improvement.

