### Study Aims

The first aim of this study is to evaluate the efficacy of an instructed mimicry task condition to improve FEER compared to a control condition and also from baseline to posttest in adults with and without alexithymia and ASD. The second aim of the study is to confirm findings by Cook et al [32] that FEER is related to alexithymia and not ASD. As an ancillary aim, the study will also collect data for further research on how eye-gaze patterns in type 1 alexithymia and type 2 alexithymia uniquely relate to FEER in the same sample.

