## Methods

### Study Design

The study design is a mixed factor 2x2x2 within-between design. Participants who meet inclusion and exclusion criteria will be randomized to a control task or the experimental task. Inclusion and exclusion criteria and pretrial control variables will be collected during an online screening stage and during an in-person clinical interview. Baseline outcomes will be assessed directly before the control task or experimental task. They will then be assessed again during the control and experimental tasks. The study will conclude with a brief measure of satisfaction of the task and a debriefing session. See Multimedia Appendix 1 for a step-by-step workflow of a participant through the study.

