### Comparator/Control Group

This study includes both a before-after, within-group comparator and a between-groups control group. To make the before-after comparison, participants will first partake in a baseline assessment task of emotion recognition before randomization to one of the experimental conditions. This baseline assessment task will be the same as the intervention task; however, participants will not be instructed to mimic the facial expressions prior to selecting an expression.

In addition to the before-after comparator, there will be a control condition. The control condition will also undergo the baseline assessment task; however, instead of participating in the mimicry intervention task, they will undergo a similar task with no mimicry element. This task will be identical to the instructed mimicry intervention task; however, instead of being instructed to mimic the facial expression, they will be instructed to “pay particular attention to the entire face prior to selecting an expression.” This instruction is aimed to match for attention levels.

A final point of comparison will be that participants will be first broken up into 2 groups, namely the AM group and ASD group. This comparison will provide the ability to analyze if any intervention effects only occur or are stronger in people with ASD, alexithymia, or the general population. The participant flow diagram can be seen in Figure 3.

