### Statistical Analyses

The data will be analyzed using SPSS, Version 25. Alexithymia will be analyzed to aid in matching the AM group and ASD group on alexithymia. To ensure that the ASD and AM groups, and also the experimental and control groups, are comparable, means and standard deviations of participant characteristics will also be compared with tests of difference.

The study design is a mixed factor, 2x2x2, within-between design (see Table 2), and therefore, the most appropriate test of difference is a mixed factorial ANOVA, set up according to Table 2 with IQ, depression, and anxiety variables added as covariates. This will provide analyses of whether the instructed mimicry intervention task was effective by comparing baseline scores to posttest scores. Additionally, it will provide the ability to compare posttest scores between the control group and the intervention group. Finally, this analysis will have the additional ability to discern these differences based on group (ASD group and AM group).

In addition to the mixed factorial ANOVA, a hierarchical regression analysis will also be conducted (see Table 3) to determine the predictive ability of alexithymia on the primary outcome variable.

**Table 2 table2:** Experimental group and intervention design.

Time point	ASD^a^ group (n=~32)		AM^b^ group (n=~32)	
	Control task condition (n=~16)	Mimicry task condition (n=~16)	Control task condition (n=~16)	Mimicry task condition (n=~16)
Pretest	FEER^c^ task score	FEER task score	FEER task score	FEER task score
Posttest (the intervention task is the posttest)	FEER task score	FEER task score	FEER task score	FEER task score

^a^ASD: autism spectrum disorder.

^b^AM: alexithymia-matched general population.

^c^FEER: facial emotion expression recognition.

**Table 3 table3:** Hierarchal regression stages for analysis.

Stage	Variables
Stage 1	IQ, age, gender
Stage 2	+Autism
Stage 3	+Alexithymia
Stage 4	+Intervention

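### Uncontrolled before-after change is one of two unranked primary metrics and is taken as evidence that mimicry works, so a practice gain alone could count as efficacy

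*Protocol article*

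**What the plan says.** Three sections of the protocol article give before-after change a role in judging efficacy.

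- **Study Aims** sets the efficacy aim as "to improve FEER compared to a control condition and also from baseline to posttest".
- **Primary Outcome** defines the first measure as "comparing the percent of correctly identified facial emotion expressions from the baseline assessment task to the instructed mimicry experimental task". It then adds a comparison of the control and intervention conditions and concludes: "This will provide 2 primary metrics: before-after percent improvement and control group to experimental group percent improvement". It gives no order between the two and no rule for combining them.
- **Statistical Analyses** says of the mixed factorial ANOVA: "This will provide analyses of whether the instructed mimicry intervention task was effective by comparing baseline scores to posttest scores". The comparison with control follows as an addition: "Additionally, it will provide the ability to compare posttest scores between the control group and the intervention group".

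Two sections show what the before-after change is made of.

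- **Study Design**: "Baseline outcomes will be assessed directly before the control task or experimental task".
- **Comparator/Control Group**: "This baseline assessment task will be the same as the intervention task; however, participants will not be instructed to mimic the facial expressions". The randomised control condition does the same baseline and then a matching task with an attention instruction in place of mimicry.

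Two sections bear on the other side. **Hypotheses** puts first the prediction that the mimicry condition improves more than the other condition, with improvement defined as posttest minus baseline. **Intervention** says that baseline and experimental pictures should be similar in recognition difficulty and refers to Multimedia Appendix 3 for how they were chosen.

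**The concern.** Everyone completes the recognition task and then completes it again straight afterwards. A second attempt may be better because the participant knows the format, the response buttons and the timing. That gain would appear in both arms and has nothing to do with mimicry. A before-after test within the mimicry arm cannot separate the two sources; the comparison with the randomised control can.

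Because the two metrics are unranked and the analysis text ties effectiveness to baseline against posttest, someone following these two sections literally could report success on the first metric while the controlled comparison shows nothing. At stake is a false efficacy claim on a primary outcome, for a task that the Discussion suggests could be used at home.

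**Working it through.** **1. The plan's own figure.** Sample Size Calculation gives f² = 0.27, 5% significance, 80% power and N = 58. An omnibus regression test with the six Table 3 predictors (IQ, age, gender, autism, alexithymia, intervention) has λ = f² × N = 0.27 × 58 = 15.66 on 6 and 58 − 6 − 1 = 51 degrees of freedom. Its power is 0.808, and 58 is the smallest N reaching 0.80. So 58 reproduces for that test, and 58 × 1.10 = 63.8 gives the stated 64. Nothing below depends on this figure being right or wrong; it supplies only the numbers per arm.

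**2. What each metric estimates.** Let P be the mean gain from repeating the task and M the added effect of mimicry over the control instruction.

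- Change in the mimicry arm = P + M
- Change in the control arm = P
- Difference between conditions = (P + M) − P = M

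The first primary metric therefore estimates P + M. With M = 0 it tests whether P is zero, which is not the efficacy question.

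**3. Inputs for the size.** Table 2 has about 16 per cell, so 16 + 16 = 32 in the mimicry condition; 58/2 = 29 if only the required number complete. The test is taken as two-sided at 5%. The practice gain is expressed as dz = P / (SD of change). The article does not give it, so a range is shown.

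**4. Formula.** For a paired t test with M = 0, the noncentrality is δ = dz × √n and the chance of significance is P(|T| > t₀.₉₇₅,ₙ₋₁), with T noncentral t on n − 1 degrees of freedom. With n = 32, √32 = 5.657, so δ = 1.131, 1.697 and 2.828 at dz = 0.2, 0.3 and 0.5.

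**5. Results when mimicry does nothing.** The first two result columns are exact. The last two come from 20,000 simulated trials with two arms of 32 and the same practice gain in each.

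| Assumed practice gain (SD of change) | Before-after, mimicry arm, n=32 | Same, n=29 | Between-condition difference in improvement | Either metric significant |
|---|---|---|---|---|
| 0 | 5% | 5% | 4.9% | 8% |
| 0.2 | 19.5% | 18.0% | 5.0% | 23% |
| 0.3 | 37.6% | 34.5% | 5.2% | 41% |
| 0.5 | 78.2% | 73.9% | 4.9% | 80% |
| 0.8 | 99.2% | 98.6% | 5.0% | 99.5% |

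The between-condition test holds its 5% level whatever the practice gain, because P cancels. With no practice gain at all, two unranked metrics each tested at 5% still give 8%.

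**6. Does any other section close the gap?** Picture matching deals with one set being easier than the other; it does not deal with having done the task before. The first hypothesis is a controlled comparison, but it does not say that the before-after metric is descriptive or needs confirmation against control. No other section says so.

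**The case against.** The strongest reply is that the trial already contains the right test. The control is randomised and does the same two-step sequence. The planned ANOVA includes the time-by-condition term, the second primary metric is between conditions, and the first hypothesis is the comparison of improvement scores. No stated hypothesis rests on uncontrolled gain. All of this stands, and it confines the fault to the definition of the primary outcome and one inference sentence. It does not remove the fault, because the hypothesis and the primary outcome now point to different tests.

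It is also fair that the practice gain is assumed. At the low end the excess is modest or nil: 5% at zero and about 20% at 0.2 SD.

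Four stronger readings are tempting, and the article does not support them.

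- **That efficacy will be judged on the pooled time effect over all 64 participants.** That would give 66% and 98% at 0.3 and 0.5 SD. But Primary Outcome defines before-after change as baseline to the mimicry task, and Statistical Analyses never names the time main effect as the efficacy test. Only the mimicry-arm figures match the definition.
- **That uncentred covariates distort the time test.** The article says only that IQ, depression and anxiety are covariates. Centring and covariate-by-time terms are left open and belong to an analysis plan. If that distortion did apply, it would also cut the pooled figures just given (to about 8% at 0.5 SD), so the two arguments cannot both be used.
- **That the two picture sets differ in difficulty.** The article states that they should be similar and refers to an appendix not shown here, so a need to swap them between time points cannot be judged.
- **That the trial has no valid efficacy test.** It has one; it is simply not given sole primary status.

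**Conclusion.** The point holds in a limited form. The article makes an uncontrolled before-after change one of two unranked primary metrics and says that effectiveness is judged from it, which conflicts with its own first hypothesis. If mimicry has no effect, the mimicry-arm test would be significant in 20%, 38% or 78% of trials at a practice gain of 0.2, 0.3 or 0.5 SD of change, against about 5% for the controlled comparison.

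These rates assume 32 participants in the mimicry arm, a two-sided 5% test, normally distributed change scores and, for the between-condition rate, the same practice gain in both arms. They are conditional: the article neither reports nor implies a particular practice effect. The structural point does not depend on its size, since before-after change estimates practice plus mimicry whatever that size is.

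**What to change.** Three wording changes, all within the protocol article's own framework:

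1. **Primary Outcome**: name the mimicry-minus-control difference in improvement as the single primary efficacy test, in line with the first hypothesis. Either the time-by-condition term or the posttest comparison adjusted for baseline would serve; state which one.
2. **Primary Outcome**: move before-after change within each arm to descriptive reporting, shown for both arms so that the control arm's gain is visible.
3. **Statistical Analyses and Study Aims**: reword the sentence that infers effectiveness from baseline against posttest, and the matching clause of the aim, so that effectiveness is inferred only from the between-condition contrast.

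The change needs no new data, no change to the task and, on this account, no change to the sample size. The Timeline states that recruitment had not begun as of June 2021. The cost is the loss of one primary metric, and it is the metric that an ineffective task could pass.

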### Intervention

The task will be delivered in-person at the Federation University Psychology Clinic in Ballarat, Australia, by the primary author in a small counselling room. The room will have 2 computers on a desk, each with separate monitors and peripherals (one for the participant and the other for recording eye-tracking data). Participants will take part in the task 1 participant at a time based on a mutually agreed upon time and date. Participants will only undergo this task once, and it is expected to take approximately 30 minutes based on prior testing where a small neurotypical group took approximately 25 minutes to complete the task in a usability test. The intervention is a software-based FEER training task that presents a series of different facial expressions and requires individuals to firstly mimic and then select which emotional expression they saw. The software runs on Microsoft Windows 10 and requires only minimal system requirements and a mouse.

The intervention task condition will begin with the software presenting a basic description of 6 facial expressions (fear, sadness, happiness, anger, disgust, surprise) and tips on how to spot each expression. Next, participants will be verbally advised by the experimenter and by on-screen text that a series of emotion recognition trials will begin shortly. Further, they will be told that after each emotion is displayed that they should try their best to mimic (copy) the observed facial expression with their own face. Once they have mimicked the expression, they should then use the 6 labelled buttons on the right-hand side (or associated keyboard shortcut) to choose which emotion was displayed. After selecting the answer using 1 of the 6 buttons, a 5-point Likert scale on the computer screen will ask the participant “How well did you mimic the expression?” with responses ranging from 1 “not very well” to 5 “very well.” This will repeat for each of the 36 trials. The trials will include various models of both men and women depicting the 6 emotions.

The sequence of each trial in the task is depicted in Figure 2 with accompanying numbered indexes. Each trial will begin with a neutral expression image displayed on the screen (index 1). After this image has been displayed for 3 seconds, it will quickly swap to another image from the same model, except this image will depict an emotional expression (eg, angry or sad, index 2). After 500 milliseconds, this image will be replaced with the original neutral image (index 3), and the 6 buttons with emotion labels will appear on the right-hand side (index 4). Once the participant selects the emotion using the 6 buttons, the trial will conclude with the 5-point rating of how well the participant felt they copied the expression (index 5).

In a task that aims to test or train FEER ability, it is important to ensure that the emotional stimuli tested against are true exemplars of the emotion they purport to signal. It is also important that the expressive images in the baseline test and the experimental tasks are similar in recognition difficulty. This will reduce the risk of improvements being attributed to easier expressions in the experimental tasks compared to the baseline task. This task used the Warsaw Set of Emotional Facial Expression Pictures (WSEFEP) [57]. See Multimedia Appendix 3 for a description of these pictures and how pictures were selected for each condition. See Figure 2 for an example of the pictures.

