**Conclusions:**

This study will be the first to evaluate the use of a novel facial mimicry task condition to increase FEER in adults with ASD and alexithymia. If efficacious, this task could prove useful as a cost-effective adjunct intervention that could be used at home and thus remove barriers to entry. This study will also explore the unique effectiveness of this task in people without an ASD, with an ASD, and with alexithymia.

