## Discussion

This paper describes, to our knowledge, the first study to assess an instructed mimicry task to increase emotion recognition ability in people with alexithymia and ASD. Despite the formulation of the alexithymia hypothesis, very few studies have assessed the impact of alexithymia in interventions aimed at increasing social functioning and in particular, emotion recognition. Additionally, to our knowledge, no other study has explored the benefits of instructed mimicry on emotion recognition in people with ASD and alexithymia. This mixed factor, 2x2x2, within-between design will assess the efficacy of the instructed mimicry task to increase FEER. This study design will enable the assessment of baseline and improvement scores individually for people with and without ASD while controlling for levels of alexithymia. This will allow analyses of how this intervention uniquely benefits ASD without the interference of alexithymia, which is known to frequently co-occur in ASD [9]. If this task is successful at increasing emotion recognition, it could provide easily accessible training to those with ASD, alexithymia, and other disorders that typically have high rates of alexithymia such as schizophrenia [59].

One proposed benefit of this intervention for people with alexithymia and ASD is that the software does not require supervision. This will likely benefit these populations as they typically enjoy computer-based interaction rather than social interaction, as indicated by previous studies (eg, [60]). This has the added benefit of improving access to the task as it could be used on a home computer, which may eliminate a key barrier to treatment.

Despite the benefits of this task and study design, some limitations are present. First, matching the ASD and AM groups on levels of alexithymia improves our ability to exclude alexithymia as a contributing factor of emotion recognition accuracy. Unfortunately, it also means that other confounding factors may have been systematically introduced when matching on alexithymia. This limitation will make it difficult to attribute any benefits of the intervention task specifically to autism. Additionally, when comparing emotion recognition accuracy, it will limit our ability to suggest whether emotion recognition difficulties are related to ASD or to alexithymia, as per the alexithymia hypothesis.

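### On the natural reading, the primary author speaks the arm-specific instruction in person just before the scored trials, so unequal delivery could enter the randomized comparison; the software could give it instead

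*Protocol article*

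**What the plan says.** The Intervention section fixes who runs the session and where: "The task will be delivered in-person at the Federation University Psychology Clinic in Ballarat, Australia, by the primary author in a small counselling room". Participants attend one at a time. Just before the scored trials, "participants will be verbally advised by the experimenter and by on-screen text that a series of emotion recognition trials will begin shortly". The text then continues: "Further, they will be told that after each emotion is displayed that they should try their best to mimic (copy) the observed facial expression". That sentence does not repeat whether the telling is oral, on screen or both.

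The Comparator/Control Group section describes the control task as the same as the mimicry task apart from the instruction: "instead of being instructed to mimic the facial expression, they will be instructed to “pay particular attention to the entire face prior to selecting an" (the quote stops one word short of the end of the sentence). Its purpose is given as "This instruction is aimed to match for attention levels". The channel is again not stated. The same section places the baseline assessment before randomization.

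Under Primary Outcome, the measure is the percentage of expressions correctly identified. Table 2 records that the intervention task is itself the posttest.

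On later use, the Discussion says: "One proposed benefit of this intervention for people with alexithymia and ASD is that the software does not require supervision". The Conclusions of the Abstract say that, if the trial succeeds, "this task could prove useful as a cost-effective adjunct intervention that could be used at home and thus remove barriers to entry".

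**The concern.** The two arms are meant to differ in one thing, the instruction. If the person who is testing the task speaks that instruction, the arms may also differ in how it is delivered: tone, emphasis, repetition, encouragement. Computer scoring keeps the experimenter from influencing the recording of an answer, but not how hard the participant tries or attends. Each expression is shown for 500 milliseconds, so attention plausibly affects accuracy. The protocol itself treats attention as a rival explanation, since it words the control instruction to match it.

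A difference that arises this way falls after allocation and inside the primary contrast. It could not be told apart from an effect of mimicry, and adjustment for a baseline taken earlier would not remove it. A second, smaller matter is what the result can support: a session run by an experimenter in a clinic says little about use alone at home.

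**Working it through.** **1. Is the arm-specific instruction spoken?**

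- The sentence that names both channels, oral and on screen, covers only the general notice that trials are about to begin.
- The mimicry instruction follows in the next sentence as a continuation, with the participant being told what to do. The same experimenter and screen carrying on is the natural reading, but it is not stated.
- For the control arm the inference has one more step: the task is otherwise identical, so the channel is presumably the same.

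**2. Would the speaker know the arm?** The article says nothing about masking the experimenter. No statement is needed for this step: a person who speaks one of two different instructions knows which one was spoken.

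**3. Can it reach the outcome?** Baseline precedes randomization, so knowledge of the arm cannot affect it. The posttest is the instructed task itself, so the posttest score can be affected. The route is participant effort or attention. Delivery that is equal in both arms does no harm; only a difference between arms biases the contrast.

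**4. The plan's own figure.** The Sample Size Calculation section gives 58 participants for f² = 0.27, 5% significance and 80% power, and 64 after 10% attrition. A noncentral F test of the overall regression with noncentrality f² × N and six predictors (the count in Table 3: IQ, age, gender, autism, alexithymia, intervention) gives N = 58 with power 0.808. Then 58 × 1.10 = 63.8, which rounds up to 64. The figure is reproduced, and the mode of instruction is not an input to it.

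**5. Scale of the outcome.** One trial is 1/36 = 2.8 percentage points. This is the value of one answer, not an estimate of bias.

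**6. What a bias would do, by assumption.** The document gives no bias, so a range is shown. Take 58/2 = 29 per arm, no true effect, a two-sided 5% test and a normal approximation. With bias b in SD units, the standard error is √(2/29) = 0.263, and

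rejection rate = Φ(b/0.263 − 1.96) + Φ(−b/0.263 − 1.96)

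| Assumed bias (SD) | Rejection rate |
|---|---|
| 0 | 5.0% |
| 0.1 | 6.7% |
| 0.2 | 11.9% |
| 0.3 | 20.8% |
| 0.5 | 47.8% |

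The article gives no SD for the score. An average of one extra correct answer (2.8 points) in one arm would equal 0.1, 0.2 or 0.3 SD if the SD were 27.8, 13.9 or 9.3 points (2.78 divided by 0.1, 0.2 or 0.3). The table shows that a modest bias would matter. It does not show that one is present.

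**7. Home use.** The statements in the Abstract, Discussion and closing summary describe possible later use, and those in the Abstract and closing summary depend on a favourable result. The Intervention section describes how this trial is run. The two are compatible, but no score in the trial is obtained without the experimenter delivering the session.

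**The case against.** The strongest case against rests on four points.

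- **The channel is inferred.** The only sentence that mentions speech concerns the general notice. A reader might take it as saying outright that the author speaks the arm-specific instruction and that the same words are on screen; the text does not say that. This stands, and the point is worded accordingly. If the instruction is not spoken, one line in the Intervention section would settle the matter.
- **Masking and scripts may be covered elsewhere.** An article commonly leaves such detail to the full protocol, and the participant workflow is in an appendix that is not shown. This stands as far as it goes: the absence of a script or a masking paragraph is not the finding. The finding is about the delivery that is described, and a masking paragraph could not conceal the arm from a person who speaks its instruction.
- **The design already limits the risk.** The control arm also receives an instruction in an otherwise identical task, the answer is a choice among six buttons, and baseline comes before allocation. All true. These features narrow the route to differential encouragement after allocation, but they do not close it.
- **There is no contradiction over supervision.** A reader might infer that in-person delivery contradicts the claim that the software needs no supervision. It does not: that claim is offered as a proposed benefit for future use, and a first evaluation in a clinic is consistent with it. What remains is that the trial does not test unsupervised use.

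A reader might also infer that the bias would favour the mimicry task because its investigator delivers both conditions. That is a reasonable expectation, but nothing in the document establishes it.

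**Conclusion.** The point holds as an inexpensive improvement to a stated method, not as a demonstrated bias. It rests on two assumptions: that the arm-specific instruction is spoken in both arms, and that effort or attention affects accuracy at a 500-millisecond exposure. Given these, unequal delivery could enter the randomized contrast for any participant in either arm and weaken the attention matching that the control instruction is there to provide. Its size and direction cannot be determined from the document, and the rejection rates above are illustrations only. The home-use statements are not contradicted by the design, but this trial will not support them directly. I rate this as a change that should be made, with medium confidence.

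**What to change.** In the Intervention and Comparator/Control Group sections:

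- Give the arm-specific instruction only through the software, as on-screen text or as a recording of equal length in both arms.
- Have the software apply the allocation after the baseline task.
- Limit the experimenter to a fixed, condition-neutral script and to rereading the screen text on request.

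If spoken delivery is kept, qualify the home-use and no-supervision statements in the Abstract, the Discussion and its closing summary as untested by this trial. They need not be removed.

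The cost is protocol wording, a small software step for the allocation and at most one short recording per arm. No participants or staff are added, and the sample size stays at 58 required and 64 recruited. The Timeline section says recruitment had not begun as of June 2021, so on that account no collected data would be affected. The small downside is less opportunity to clarify the task in conversation, which rereading the screen text partly covers.
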